## Methods

This will be a pragmatic, participant-blind, parallel-group, randomised feasibility trial comparing access to a podiatry service with usual care. The trial is registered with the Australian and New Zealand Clinical Trial Registry (ANZCTRN12625001000493) and has been developed in accordance with the SPIRIT 2025 statement [17], the CONSORT 2010 statement extension to randomised pilot and feasibility trials [18], and the TIDieR checklist for reporting of interventions [19]. Ethics approval has been obtained from the La Trobe University Human Ethics Committee (Approval number HEC25095 on the 20th of May 2025) and written informed consent will be obtained from all participants during the baseline assessment.

The randomisation module in REDCap (Research Electronic Data Capture, Vanderbilt University, USA) will be used to randomise participants. Participants will be allocated on a 1 to 1 ratio with blocking in groups of 4 and 6, and stratification based on sex at birth to ensure a balance of participant sex between the groups. Allocation will be concealed from all researchers until after eligibility screening. Participants will be randomised to their intervention after completing consent at the baseline assessment.

Given this is a feasibility trial, only participants will be blind to their allocation. Both groups will be blind to group allocation through limited disclosure. All participants will be informed that two different types of treatment are being compared, however only the intervention group will be informed about the additional access to podiatry treatment.

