### Patient and public involvement

Recognising the importance of designing patient-centred research, we included a consumer as a coauthor (KL) during the initial design of the trial and securing grant funding. To further inform the trial design, we conducted four semi-structured interviews with people who have a rheumatological condition and foot-specific complaints. These interviews aimed to gather detailed feedback on various aspects of the trial, including the acceptability of the intervention, the feasibility of the proposed procedures, potential barriers to participation, and what outcomes are important. The interviews were conducted prior to the approval of the ethics application.

Participants will be recruited from outpatient rheumatology clinics at Austin Health in Melbourne, Australia. Rheumatologists will be informed about the trial and asked to recommend that their patients consider participating if they have foot-specific symptoms. Therefore, rheumatologists will initially approach participants about participating in the study and recommend that potential participants contact the researchers via a website. To be eligible for inclusion, participants must:be adults over 18 years of age;have a diagnosis of a rheumatological condition from a rheumatologist;have foot-specific symptoms rated 3/10 or greater on a numerical rating scale (e.g. pain, stiffness, dermatological complaints); andhave experienced symptoms for at least four weeks.

Participants will be excluded if they:are unable to understand the English language in verbal or written form;have regularly attended a podiatry service for management of their rheumatological foot problem in the past 3 months;have an active bacterial infection of the foot; andexperience foot symptoms that are not related to the rheumatological condition.

The recommended sample size for feasibility studies is 12 people per group [21], however to allow for a 20% drop-out rate, we will recruit 15 participants per group. This is similar to the median sample size of 30 for pilot trials documented in the United Kingdom Clinical Research Network database [22]. Given the low-risk nature of the interventions, we are not specifying interim analyses or guidelines for stopping the trial.

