### Other variables: limited efficacy testing

In addition to evaluating feasibility, limited efficacy testing will be undertaken on measures to be included in a fully powered randomised trial. These measures are outlined briefly in Table 2 and in specific detail in Online Resources 2.

**Table 2 Tab2:** Other variables measured for limited efficacy testing

Variable	Outcome measure	Timepoints
Goal attainment	Goal Attainment Scaling	Baseline and week 12
Global change	Global Perceived Rating of Change (15-point Likert scale)	Week 6 and week 12
	Patient Global Assessment	Baseline, week 6 and week 12
Foot-specific pain	Foot Health Status Questionnaire—foot pain domain	Baseline, week 6 and week 12
	Manchester-Oxford Foot Questionnaire—foot pain subscale	Baseline, week 6 and week 12
Foot-specific function	Foot Health Status Questionnaire—foot function domain	Baseline, week 6 and week 12
	Manchester-Oxford Foot Questionnaire—walking/standing subscale	Baseline, week 6 and week 12
Disability	Health Assessment Questionnaire—disability index	Baseline, week 6 and week 12
Stiffness	11-point numerical rating scale	Baseline, week 6 and week 12
Fatigue	Functional Assessment of Chronic Illness Therapy-Fatigue (FACIT-Fatigue) version 4	Baseline, week 6 and week 12
Change in physical activity	Global Physical Activity Questionnaire	Baseline, week 6 and week 12

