### Statistical analysis

Descriptive statistics will be used to report feasibility outcomes. Mean (SD) scores and mean differences (95% CI) will be used to explore differences in continuous variables between the groups and Cohen’s *d* will be calculated to evaluate efficacy for the secondary outcome measures. A small effect size (Cohen’s *d* ≥ 0.20) will be regarded as an acceptable between group difference to signal efficacy. Data that is not continuous (adverse effects and use of cointerventions) will be reported using frequencies, medians and interquartile ranges as appropriate. Between group differences will be explored using risk ratios. Missing data will be minimised as much as possible, however no statistical approaches will be used to replace missing data. Any missing data will be evaluated and reported.

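### The planned raw differences and Cohen's d use only participants seen at the visit in question and leave unused the baseline and week-6 scores that nine of the 11 measures provide

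*Protocol article*

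**What the plan says.** The design is a "randomised feasibility trial comparing access to a podiatry service with usual care". For the efficacy measures, the Statistical analysis section says "Mean (SD) scores and mean differences (95% CI) will be used to explore differences in continuous variables between the groups", adds Cohen's d, and sets a mark: d of at least 0.20 "will be regarded as an acceptable between group difference to signal efficacy". On missing values it says "no statistical approaches will be used to replace missing data" and "Any missing data will be evaluated and reported". No repeated-measures or baseline-adjusted model is named, and no visit is attached to d.

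The sample-size paragraph (under Patient and public involvement) starts from "The recommended sample size for feasibility studies is 12 people per group" and then, "to allow for a 20% drop-out rate, we will recruit 15 participants per group". Table 1, domain 9, accepts questionnaire completion down to 75% at weeks 6 and 12.

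In Table 2, nine of the 11 measures follow the pattern of "Health Assessment Questionnaire—disability index Baseline, week 6 and week 12". The exceptions are Goal Attainment Scaling (baseline and week 12) and Global Perceived Rating of Change (weeks 6 and 12). Under Procedures, week 6 is an emailed survey and week 12 an in-person visit.

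**The concern.** A raw mean difference without replacement is an available-case comparison. It estimates the difference between the randomised groups without bias only if loss is unrelated to outcome, or related to it in the same way in both arms.

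The schedule makes loss after week 6 plausible, since an emailed survey is easier to complete than a clinic visit. Loss that differs by arm is also plausible, since only the podiatry arm has extra treatment visits. A participant lost after week 6 has already supplied two scores that help predict the third. Reporting the missingness describes it but leaves the estimate as it was.

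At stake is whether d reaches 0.20, the protocol's own efficacy signal, and how precise the estimates are in a trial meant to inform the sample size of the next one.

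**Working it through.** **Inputs from the protocol:** 12 evaluable and 15 recruited per group, 20% drop-out allowance, 75% completion floor, d mark of 0.20, visit schedule in Table 2. **Assumed, because the protocol gives no figures:** gap between stayers and leavers, correlation between visits (0.5 to 0.7), and strength of the link between loss and outcome.

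1. *Plan's own figure.* 12 / (1 − 0.20) = 15 per group, which reproduces. Conversely, 15 × 0.80 = 12 observed per arm.

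2. *Shift in d.* With f the share lost and D the stayer-minus-leaver gap in SD, in the podiatry (1) and control (0) arms, shift = f1·D1 − f0·D0.
   - 20% lost per arm, related to outcome in one arm only: D = 0.25 gives 0.05; D = 0.5 gives 0.10; D = 1.0 gives 0.20 (25%, 50% and 100% of the mark).
   - 25% lost, the limit of domain 9: D = 0.5 gives 0.125.
   - Same share and same gap in both arms: 0.20 × 0.5 − 0.20 × 0.5 = 0.

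3. *A specific mechanism.* Suppose 20% of the podiatry arm is lost after week 6, with loss correlated 0.5 with a poor week-6 score, and control loss is random.
   - By hand: removing the lowest 20% of a normal score raises the remaining mean by 0.28 / 0.80 = 0.35 SD. Then 0.35 × 0.5 × 0.5 = 0.09 at visit correlation 0.5, and 0.35 × 0.5 × 0.7 = 0.12 at 0.7.
   - Simulation (15 per arm, 3 lost per arm, true d 0.20, 20,000 replicates): available-case bias +0.084 and +0.118, or 42% and 59% of the mark. A likelihood analysis using baseline and week 6: +0.002 in both cases.
   - Same mechanism in both arms: available-case bias between −0.005 and +0.007.
   - Loss driven by the unseen week-12 value in one arm (large-sample calculation, true d 0): an available-case shift of about 0.18 falls only to 0.12 (correlation 0.5) or 0.09 (correlation 0.7) when the earlier scores are used.

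4. *Against noise.* With 12 per group, SE of d ≈ √(2/12) = 0.41, and the 95% half-width is about 0.85. The bias in step 3 is therefore 0.08/0.41 to 0.12/0.41, about 0.2 to 0.3 SE. If the true effect is zero, d reaches 0.20 about 31% of the time without bias and about 41% with a shift of 0.10.

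5. *Precision under random loss.* Both methods are then unbiased. The simulated SE is about 0.40 for the raw comparison, against 0.36 (correlation 0.5) and 0.29 (correlation 0.7) for the likelihood analysis; under the mechanism in step 3 the latter are 0.36 and 0.30. Baseline adjustment alone explains most of the gain: √(2 × (1 − 0.5²)/12) = 0.35 and √(2 × (1 − 0.7²)/12) = 0.29. Week 6 contributes the removal of bias rather than the precision.

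**The case against.** The strongest reply is that this is a feasibility trial with descriptive, explicitly limited efficacy testing and no hypothesis test, and that model detail may sit in an analysis plan that is not shown. Proportion is a fair point and keeps the matter modest. But the article does name an estimator and a mark, so the available-case reading comes from what is written rather than from missing detail. It remains an inference, as does week 12 as the time of d.

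The size of the bias is also conditional. It needs loss that works differently in the two arms, and the protocol gives no figure for that. The 20% is a recruitment allowance, not a forecast.

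Three stronger readings are tempting and not supported:
- A reader might infer that the missing-data sentence rules out all statistical handling. It bars only replacing values; a likelihood model replaces none.
- A reader might infer that participants who stop treatment are excluded. The protocol says no such thing; someone who stops podiatry visits can still give week-12 data.
- A reader might infer that drop-out would decide whether efficacy is signalled. Sampling error is three to five times the simulated bias (0.41/0.12 to 0.41/0.08).

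Finally, a repeated-measures model does not reach everything. Goal Attainment Scaling, the candidate primary outcome, has no week-6 score, and Global Perceived Rating of Change has no baseline.

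**Conclusion.** The concern holds in a limited form. As naturally read, the plan compares raw available-case means and passes over earlier scores held for nine of 11 measures. Under arm-specific, outcome-related loss at the 20% allowance, with visit correlations of 0.5 to 0.7, d shifts by about 0.08 to 0.12 against a mark of 0.20; under identical mechanisms it does not shift. That can tip the signal without deciding it. The loss of precision is the firmer part: it needs no assumption about why people leave, only that visits are correlated. This is a worthwhile improvement to the efficacy analysis. It does not threaten the feasibility outcomes.

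**What to change.** In the Statistical analysis section:

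- For the nine measures taken at baseline, week 6 and week 12, estimate the between-group differences from a likelihood-based repeated-measures model with group, visit, group-by-visit and baseline, using every observed score.
- State the visit to which d refers and which SD standardises it. The choice matters: the symptom threshold for entry may narrow baseline SDs, which would raise a d scaled by them.
- Report the raw available-case d alongside.
- For Global Perceived Rating of Change, use the same model without its own baseline.
- For Goal Attainment Scaling, keep the observed-data estimate and add one sensitivity estimate with missing week-12 goals scored at their baseline level.

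The missing-data sentence can stand for the main estimates. It needs a short exception for the Goal Attainment Scaling sensitivity line, which does fill in values.

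The cost is some wording and a few lines of code, with no new data or participants. The model assumes that loss is explained by observed scores, does not fully handle loss before week 6, and is slightly less simple to present than raw means.

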## Discussion

This study aims to assess the feasibility of conducting a pragmatic randomised trial to evaluate the effectiveness of a publicly-funded podiatry service for people with foot-related symptoms due to rheumatological conditions. The study will also explore the appropriateness of using patient-centred goal-setting as an outcome measure. People with rheumatological conditions often experience severe foot-related symptoms that significantly impact their daily lives. Despite advancements in treatment, these symptoms may persist, highlighting the need for ongoing multidisciplinary collaboration to improve patients’ health and wellbeing. There is a notable lack of podiatric care within multidisciplinary teams in Australia [14], which is crucial for optimal management of these foot-related issues.

One UK-based randomised trial has evaluated podiatry care for people with rheumatoid arthritis [24]. This exploratory trial randomised participants to receive podiatry-led foot care for 12 months or a no treatment control group. The authors reported several considerations for the design of future fully powered randomised trials that we have considered during the design of this trial. First, the findings suggest that podiatry-led foot care maintains but does not improve foot-related impairment or disability in patients with stable, controlled rheumatoid arthritis. These findings suggest that podiatry-led care is important for maintaining foot health. A consideration for these findings was the use of a standardised outcome measure (the Leeds Foot Impact Scale) that may not be responsive to change [25]. Therefore, selecting an outcome measure that is both meaningful for patients and sensitive and responsive is important. Our feasibility trial includes multiple patient-centred outcome measures to allow evaluation of their performance for a larger randomised trial. Second, the trial faced difficulties recruiting participants due to stringent criteria for stable drug management and co-morbid diseases such as diabetes and peripheral vascular disease. The authors reported the criteria were too strict and therefore excluded many potential participants. For our feasibility trial, the inclusion criteria are broader and include any rheumatological condition without excluding participants with comorbidities. Third, more than one-third of patients refused to participate in the trial, mainly due to additional clinic visits, lack of understanding of podiatry care, and concerns about the non-intervention arm. Clear communication about the benefits and risks of podiatry care is therefore essential.

One objective for this feasibility trial is to evaluate the feasibility of using patient-centred goal attainment outcome measures (Goal Attainment Scaling). Goal Attainment Scaling is a structured method used to set and measure the achievement of patient-centred goals. The overall effectiveness of the intervention is determined by aggregating individual goal scores into a single t-score. Goal Attainment Scaling has several benefits, such as allowing patient-centred outcomes, greater sensitivity to change compared to standardised measures, and flexibility in settings with heterogenous participants. However, there are some challenges when implementing Goal Attainment Scaling in a randomised trial, such as ensuring consistent goal-setting across different practitioners, managing patient expectations, and dealing with the subjective nature of goal assessment [26].

This protocol outlines the methods for a participant-blinded, parallel-group randomised feasibility trial to compare the addition of a podiatry service to usual care for people with a rheumatological condition and foot specific symptoms. In addition to determining whether a larger randomised trial is feasible, this trial will also evaluate whether it is feasible to use Goal Attainment Scaling as a primary outcome measure and provide data to determine a suitable sample size.
